**Controlled interrupted time series (CITS)**

This CITS study will be conducted over 72 months and includes three distinct periods: a 49-month pre-intervention period (2020-2023), a 4-month intervention period and a 19-month post-intervention period (2024-2025). ITS is a quasi-experimental design for assessing public health interventions and is a robust method when other designs such as randomised controlled trials are impractical. ITS study designs allow adjustment of potential biases such as secular trends, seasonal trends, random fluctuations, and autocorrelation compared to other quasi-experimental designs such as controlled before and after studies.
^
34
^ Inclusion of a control group can strengthen an ITS evaluation by allowing assessment of whether any observed impact of the intervention is likely causal, or could instead be due to co-interventions or other events occurring concurrently with the intervention.

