**Intervention and control populations**

The social media campaign will be targeted to Aboriginal young people in the Perth region. The control group will be non-Aboriginal young people in the same location. We have chosen this characteristic-based control group because we expect that any co-interventions or concurrent events would likely affect both groups.
^
35
^ Therefore, if an impact is observed in both groups, this suggests it may be due to a co-intervention/concurrent event, while if the impact is only observed in the intervention series, this suggests the effect is more likely to be due to the intervention. During the intervention delivery we will collect information on events and interventions that occurred within Perth to improve HPV vaccination rates and who were the target population. We will report these in our final publication.

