**Sample size**

Based on data from the Australian Bureau of Statistics, we anticipate approximately 89 Aboriginal youth turning 15 years old each month in Perth over the study period.
^
32
^ Using the primary outcome definition, monthly numbers of young people before their 15
^th^ birthday fully vaccinated against HPV, will be the unit of aggregation in the regression models. A total of 72 monthly data points (2020-2025) will provide 85% power to detect a one-standard-deviation shift in the average proportions post-intervention, at an α = 0.05 and a first-order autoregressive model with autocorrelation of 0.3.
^
38
^ Empirical research has shown autocorrelations of the order of 0.3 (median 0.33; IQR 0.03, 0.58; 36 ITS studies in public health).
^
39
^

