**Data analysis**

*Interrupted time series*

A linear, segmented interrupted time series analysis will be used to evaluate the impact of the social media programme on HPV vaccination.

For the primary outcome, we will count the number of youths aged between 12 and before their 15
^th^ birthday who have received the HPV vaccination per month. Similarly, for the secondary outcome, we will count the number of young people aged up to 25 (inclusive) who have received the HVP vaccination per month. Our analysis models will include two segments: a pre-interruption period of 49 months, beginning on Jan 2020-Dec 2023, and a post-interruption period of 24 months, beginning on Jan 2024-Dec 2025, which encompasses both the intervention and post-intervention periods.

For each outcome, we will fit the following statistical model (Model 1), separately for the intervention and control series:

$$\text{Model}\;1:\log Y_{t}=\beta_{0}+\beta_{1}t+\beta_{2}I+\beta_{3}\left(t-T_{I}\right)I+\text{seasonal}+\text{offset}+\epsilon_{t}$$
where

$Y_{t}$
 is the outcome value at time t, and

$T_{I}$
 is the time of the interruption. The variable

I
 indicates the post-interruption segment, which is equal to 1 post the interruption and 0 before. Parameter

$\beta_{0}$
 is the intercept at the beginning of the series,

$\beta_{1}$
 is the slope in the first segment,

$\beta_{2}$
 is the level change between the expected value (based on the pre-interruption data) and the observed data, and

$\beta_{3}$
 is the difference in slope compared to

$\beta_{1}$
. The error term,

$\varepsilon_{t}$
 represents deviations from the fitted model, and we will assume these to have lag-1 autocorrelation. Seasonality will be accounted for by including two pairs of sine and cosine harmonics with periods of 12 and 6 months.
^
40,
41
^ Due to the changing of the vaccine schedule in the year following the interruption, the seasonal components will be phase shifted by six months for that year. The log of the relevant population (i.e. all Aboriginal youth aged between 12 and before their 15
^th^ birthday per month) will be included as an exposure offset to adjust for any changes to the population over time. We will assume a negative binomial distribution with a log link function. We will fit these models using the glarma package in R.
^
42
^

The effect measures of interest will be:

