•Level change at the end of the social media campaign (i.e. three months post the beginning of the social media campaign).•Change in slope.

In addition to the above model, for both outcomes, we will also fit the following single model (Model 2) that incorporates both the intervention and control series:

$$\text{Model}\;2:\log Y_{t}=\beta_{0}+\beta_{1}t+\beta_{2}I+\beta_{3}\left(t-T_{I}\right)I+\beta_{4}G+\beta_{5}\mathrm{tG}+\beta_{6}\mathrm{IG}+\beta_{7}\left(t-T_{I}\right)\mathrm{IG}+\text{seasonal}+\text{offset}+\epsilon_{t}$$
where

$Y_{t},T_{I},I,t,\text{seasonal},\text{offset and}\;\epsilon_{t}\;$
are as described above.

G
 represents the series with a value of 1 representing the intervention series, and a value of 0 representing the control series.

$\beta_{0}$
,

$\beta_{1}$
,

$\beta_{2}$
 and

$\beta_{3}$
 are as described above for the control series.

$\beta_{4},\beta_{5},\beta_{6}\;\text{and}\;\beta_{7}$
 represent the interactions between time and the intervention series. Specifically,

$\beta_{4}$
 represents the difference in the intercept at the beginning of the series between the intervention and control series,

$\beta_{5}$
 represents the difference in slope between the intervention and control series in the first segment,

$\beta_{6}$
 represents the difference in the level change between the intervention and control series, and

$\beta_{7}$
 represents the difference in the change in slope between the intervention and the control series.

We will compare the estimates of level change at the end of the social media campaign and change in slope between Model 1 and Model 2. This comparison will allow us to assess the possibility of whether a co-intervention/concurrent event may explain our findings.
^
35
^

We will plot interrupted time series graphs for all outcomes and series using the recommendations of Turner et al.
^
43
^ These plots will include: data points, trend lines, seasonality estimation and confidence intervals surrounding the trend line and counterfactual estimates. Segments will clearly delineated by breaks in the trend lines.

Subgroup analysis

We will fit Model 1 for the primary and secondary outcomes for the intervention series separately by:
•Sex (Females, Males)•Location in Perth (North West, North East, Central, South West and South East)

Influencer data

All qualitative information will then be synthesised descriptively, key messages will be identified, with thematic analysis completed using Nvivo software.

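### The sex and location analyses are separate, uncontrolled fits, so they neither test whether the campaign effect differs between subgroups nor separate each subgroup's effect from concurrent events

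*Protocol article*

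**What the plan says.** In the protocol article, the Subgroup analysis paragraph of Data analysis reads: "We will fit Model 1 for the primary and secondary outcomes for the intervention series separately by" sex, with two levels, and location in Perth, with five. Model 1 is the single-series segmented regression. It has an intercept, trend, level change, slope change, harmonics and a population offset, and no term for a control series or a subgroup.

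The controlled model is planned for the two outcomes overall: "we will also fit the following single model (Model 2) that incorporates both the intervention and control series". It is not named for the subgroups.

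The article gives its reason for a control in the section on the controlled interrupted time series: "Inclusion of a control group can strengthen an ITS evaluation by allowing assessment of whether any observed impact of the intervention is likely causal". Under Intervention and control populations it states the attribution rule: "if the impact is only observed in the intervention series, this suggests the effect is more likely to be due to the intervention". Under Data collection, sex and address postcode are part of a data request that covers both Aboriginal and non-Aboriginal people.

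**The concern.** There are two separate defects.

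**No contrast between subgroups.** The usual reason to analyse by sex or area is to ask whether the effect differs. Separate fits answer a different question, namely what the effect is in each stratum. Without a contrast, the natural shortcut is to compare which fits reach significance. That comparison often shows a difference when none exists.

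**No control within subgroups.** The design attributes an effect to the campaign by setting the intervention series against the control series, and the subgroup analyses drop that step. This matters because the article itself reports a concurrent change: "Due to the changing of the vaccine schedule in the year following the interruption", the seasonal terms are to be phase shifted. An uncontrolled subgroup estimate cannot separate the campaign from an event of this kind.

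The stake is practical. The Introduction notes that boys have been neglected in research on barriers to uptake, and the Dissemination section foresees carrying the model to other communities and populations. A spurious finding that the campaign worked in one sex or one area could misdirect that work.

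**Working it through.** **Inputs from the article.** 72 monthly points, α = 0.05 (taken as two-sided), lag-1 autocorrelation 0.3, a shift of one standard deviation, and stated power of 85% (Sample size). The segments are taken as 48 + 24 months, because January 2020 to December 2023 is 48 months although the text says 49. There are two sex levels and five locations.

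**Assumptions.** The documents give no subgroup sizes or variances. Subgroups are taken as equal in size and independent, with the same true effect in each.

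**Step 1: reproduce the stated power.** For a simple before/after shift in the mean under AR(1) with ρ = 0.3, the generalised least squares standard error is 0.332 SD. Power = Φ(1/0.332 − 1.96) = 85.4%, which matches the stated 85% (84.6% with 49 + 23 months). This applies to the whole intervention series. No power is stated for subgroups.

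**Step 2: whole-series power for Model 1's own level change.**
- With trend and slope-change terms, at the interruption: SE 0.622, power 36%.
- With harmonics added and evaluated at three months, the article's effect measure: SE 0.598, power Φ(1/0.598 − 1.96) = Φ(−0.288) ≈ 39%.

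**Step 3: power in each sex.** If sampling noise dominates, halving the counts multiplies the standard error by √2.
- From 85%: the effect divided by its standard error is 1.960 + 1.036 = 2.996. Then 2.996/√2 = 2.119, and power is about 56%.
- From 39%: (1/0.598)/√2 = 1.672/1.414 = 1.182, and power is about 22%.
- From 36%: (1/0.622)/√2 = 1.608/1.414 = 1.137, and power is about 21%.

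**Step 4: chance that exactly one sex is significant.** With power p in each, this is 2p(1 − p).

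| Power assumed in each sex | Chance of disagreement |
|---|---|
| 85% (standard error does not grow) | 2 × 0.85 × 0.15 = 26% |
| 56% (from 85%, scaled by √2) | 2 × 0.563 × 0.437 = 49% |
| 22% (from 39%, scaled by √2) | 2 × 0.22 × 0.78 = 34% |
| 21% (from 36%, scaled by √2) | 2 × 0.206 × 0.794 = 33% |

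**Step 5: five locations.** The chance that the fits do not all agree is 1 − p⁵ − (1 − p)⁵. Starting from 85% and scaling by √5 gives p ≈ 27% and 79% disagreement. With no growth in the standard error it is 56%. Starting from 36% it is about 44%.

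**Step 6: what an interaction test could detect.** If each sex has a standard error √2 times the whole-series value, their difference has one √2 × √2 = 2 times as large. For a sex difference as large as the whole 85%-powered effect, power = Φ(2.996/2 − 1.96) = Φ(−0.462) ≈ 32%. From the 39% base it would be about Φ(1.672/2 − 1.96) = Φ(−1.124) ≈ 13%. Neither figure allows for added noise from the control series.

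**The case against.** The strongest reply is that the protocol promises no differential claim. Its hypothesis is about the overall effect, no rule reads subgroups by significance, and the plots will carry confidence intervals. That is right, and it limits the point to what the results could be taken to mean. A reader might infer that the investigators intend to declare a difference by sex or area, but nothing in the article says so.

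Several other points stand in whole or in part.

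- **A contrast is recoverable.** Each fit gives a log-scale coefficient and standard error, so an approximate difference can be computed afterwards. However, the plan does not name one. Simple subtraction also treats the strata as independent although they share calendar months, and separate fits supply no covariance.
- **The disagreement figures depend on assumptions.** It is tempting to apply the 39% to each sex, which gives 2 × 0.39 × 0.61 = 48%. But 39% belongs to the whole series, and lower power below one half reduces disagreement. Scaling for halved counts gives about 34%. Positive correlation between the sexes would lower it further.
- **Missing control is not a source of chance differences.** A concurrent event that affects all subgroups alike largely cancels in a between-subgroup contrast. The control matters for the effect within each subgroup and for events specific to one subgroup.
- **Sparse location counts.** The article says "we anticipate approximately 89 Aboriginal youth turning 15 years old each month in Perth over the study period", and 89/5 ≈ 18 per area might be read as the size of each location series. That figure is a birthday cohort. Model 1 counts vaccinations among all those aged 12 to under 15, with that population as the offset, so 18 is not its denominator.
- **Multiplicity.** Seven subgroups, two outcomes and two measures give 28 estimates, but the article does not specify 28 tests. A multiplicity rule or exploratory label can be left to the analysis plan, so its absence here is not the point.

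The reply does not remove the core. The article fixes the model, the series and the separate fitting, and nothing elsewhere offsets that choice.

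**Conclusion.** The point holds in a limited form. As written, the subgroup plan gives no between-subgroup estimate or test, and it leaves subgroup effects without the control on which the design rests attribution. With identical true effects, the two sex fits would disagree on significance in about 26% to 49% of cases, and in about 34% on the scaled Model 1 basis. For five locations the range is about 44% to 79%. These figures assume equal, independent subgroups, a normal approximation, and the article's one-SD shift and autocorrelation of 0.3.

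The documents do not support reading this as a planned false claim or as a flaw in the main evaluation: the primary analysis is unaffected. It is a stated method with a better alternative at little cost, and it should be changed.

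**What to change.** For each factor, replace the separate fits with one extended Model 2. With S for subgroup, add S × I × G and S × (t − T_I)I × G together with their lower-order terms: S, S × t, S × I, S × (t − T_I)I, S × G and S × t × G. Use subgroup-specific population offsets in both populations.

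Report the between-subgroup ratios of level change and slope change with confidence intervals, and one joint interaction test per factor. Label them exploratory. Subgroup-specific effects can still be shown, taken from this model. Sharing seasonal or autocorrelation terms across locations is optional: it saves parameters but imposes a restriction that would need checking.

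The cost is revised wording and modest extra analysis. Sex and postcode are already in the data request for both populations. The drawback is low interaction power, about 32% even for a sex difference as large as the whole 85%-powered effect. The plan should therefore say that a non-significant interaction test will not be read as equal effects.

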### Dissemination

Part of the outcomes of this project will be a brand that will be associated with the HPV vaccine. It is expected this brand will organically be distributed amongst Influencers and their followers. We will also circulate the brand to health services and other organisations through collaborations with Aboriginal organisations. If this model is successful in improving HPV vaccination rates, the process of creating these improvements, the development of a public health model that engages young Aboriginal people to improve their health outcomes, will be easily translatable to other Aboriginal communities, health outcomes and populations. We will have developed a step-by-step guide on how to complete this, including branding that can be used by any young person or Influencer.

### Study status

Intervention started Feb 2024.

## Discussion

This project aims to improve HPV vaccination rates amongst young Aboriginal people. Nationally, 75% of Aboriginal females and 68% of Aboriginal males receive their full course of the HPV vaccine at 15 years of age, however, there is substantial variation between states and territories. Given that the vaccine reduces the risk of cervical cancer, which has a high mortality rate in Aboriginal women, improving HPV vaccine rates is essential. Our project will combine health messages co-created by young people and implemented by micro-Influencers to improve HPV vaccination. Our vision is to develop campaign that can be implemented by other Aboriginal communities, settings and populations across Australia to improve HPV vaccination.

## Ethical considerations

Approvals were obtained from the Western Australian Aboriginal Health Ethics Committee (WAAHEC Ref No: 1227) and Edith Cowan University (2022-03993 [name]). This study adheres to the Declaration of Helsinki.

## Consent to participate

Consent was received for all interviews conducted all participants. Interviews with young people and families required written consent. Interviews with influencers required verbal. Verbal consent was approved as Influencers are located around Australia and we were unable to complete face to face interviews, therefore online interviews were completed. Verbal consent for these was ethically approved. Ethics has been approved for all consent processes described. For HPV vaccine data a waiver of consent was approved to receive these data.

## Data Availability

No data is associated with this article. We will provide full PICFs and interview guides on request and if approved by our governance group. We have provided the SPIRIT guidelines in Figshare (
https://doi.org/10.6084/m9.figshare.29833178.v5)
^
45
^ and amended as needed for this study design.
^
44
^ We have also provided an example PICF and interview guide. We will provide full PICFs and interview guides on request and if approved by our governance group.
